## Abstract

**Background:**

Opportunistic recruitment is a highly laborious and time-consuming process that is currently performed manually, increasing the workload of already busy practitioners and resulting in many studies failing to achieve their recruitment targets. The Translational Medicine and Patient Safety in Europe (TRANSFoRm) platform enables automated recruitment, data collection and follow-up of patients, potentially improving the efficiency, time and costs of clinical research. This study aims to assess the effectiveness of TRANSFoRm in improving patient recruitment and follow-up in primary care trials.

**Methods/design:**

This multi-centre, parallel-arm cluster randomised controlled trial will compare TRANSFoRm-supported with standard opportunistic recruitment. Participants will be general practitioners and patients with gastro-oesophageal reflux disease from 40 primary care centres in five European countries. Randomisation will take place at the care centre level. The intervention arm will use the TRANSFoRm tools for recruitment, baseline data collection and follow-up. The control arm will use web-based case report forms and paper self-completed questionnaires. The primary outcome will be the proportion of eligible patients successfully recruited at the end of the 16-week recruitment period. Secondary outcomes will include the proportion of recruited patients with complete baseline and follow-up data and the proportion of participants withdrawn or lost to follow-up. The study will also include an economic evaluation and measures of technology acceptance and user experience.

**Discussion:**

The study should shed light on the use of eHealth to improve the effectiveness of recruitment and follow-up in primary care research and provide an evidence base for future eHealth-supported recruitment initiatives. Reporting of results is expected in October 2015.

**Trial registration:**

EudraCT: 2014-001314-25

## Introduction

### Background

Recruitment to primary care trials is a particularly challenging process with most studies struggling to reach their recruitment targets. In fact, a survey of authors of 39 published primary care trials found that only 29% of UK primary care studies achieved their recruitment targets within the agreed timeframe, with 70% requiring additional time to recruit the predefined number of participants [1]. This is very worrying considering that clinical trials succeed or fail based on whether they manage to recruit the sufficient number of participants to enable researchers to generate accurate results to precisely and reliably answer the question at hand. Recruitment failings can result in studies lacking statistical power to produce significant results, increasing the risk that an effective health intervention will be abandoned before its real impact has been demonstrated [2]. Consequently, improving the recruitment process in clinical trials is extremely important for the future of medical research.

Evidence suggests that the most effective method of recruitment in primary care is opportunistic recruitment [3]. This involves approaching eligible primary care patients when they visit their general practitioner (GP) and inviting them to take part. Opportunistic recruitment takes place in a highly stressful and time-pressured clinical environment and relies on busy GPs directly inviting patients within the consultation [4]. As a result, this method can be very challenging and slow with practitioners often failing to translate the initial enthusiasm into recruitment targets [5].

The increased adoption of electronic health records (EHR) systems in primary care provides the opportunity for real-time identification of eligible participants through the use of clinical trial alert systems [6-9]. Such systems notify GPs about eligible patients during the consultation allowing them to immediately discuss the trial with the patient to enable instant recruitment, thus negating the need for laborious effort on the part of the practitioner, patient or researcher [10]. The Translational Medicine and Patient Safety in Europe (TRANSFoRm) project team has developed a suite of software tools and underlying infrastructure to support patient recruitment to primary care studies across multiple sites and countries, potentially saving time for busy practitioners and patients in the consultation room [11]. This protocol describes a cluster randomised controlled trial evaluating the effectiveness of the TRANSFoRm system in improving patient recruitment and follow-up in primary care trials.

The TRANSFoRm system supports secure, provenance-enabled design, deployment and collection of patient-reported outcome measures (PROM) and electronic case report forms (eCRF) through web and mobile applications as well as EHR systems in the primary care centres where the trials are taking place, as shown in Figure 1. The GP-facing tools enable automated identification, eligibility check, randomisation, baseline and follow-up data collection and reporting of data in clinical studies, while the patient-facing tools support collection of patient-reported data through mobile or web applications.

**Figure 1 Fig1:**
[figure not shown]
**TRANSFoRm system components.**

Figure 2 shows the TRANSFoRm-supported clinical trial workflow, starting with a patient visiting their GP for their consultation. Potential participants are identified using a clinical trial alert tool that notifies the GP that the patient fulfils specific inclusion criteria, after checking for diagnoses, symptoms and/or treatment prescriptions. Once identified, the GP can check for the first set of inclusion and exclusion criteria and, if the patient is still suitable, collect informed consent for further screening. Next, clinical data from the patient’s electronic record is extracted to populate fields in the eCRF. The system alerts the practitioner about any missing data and presents the study dataset for final approval. PROM data is incorporated into the eCRF via a web or mobile application used by participants to record symptoms, signs and other self-reported outcomes. The system randomises enrolled patients and reports allocation instantly so that the study intervention can be initiated without delay. Participants are then followed up using the mobile or web applications and the eCRF tool at GP visits. Following GP approval, the study dataset is delivered to the researcher through a secure data transport mechanism that communicates with TRANSFoRm connector tools on the participating EHR.

**Figure 2 Fig2:**
[figure not shown]
**TRANSFoRm clinical trial workflow.**

The development of the clinical study workflow has been structured around a clinical study which acts as a use case for the evaluation of TRANSFoRm. The gastro-oesophageal reflux disease (GORD) study employs a randomised controlled trial design to answer the following question: “*What gives most symptom relief and improvement in quality of life in patients with GORD, on demand or continuous use of proton pump inhibitors?*”. Participants will be patients with GORD, aged 18–65 years old. The study will take place in five countries and will involve 16-week recruitment and 8-week follow-up. The follow-up time was chosen because proton pump inhibitor (PPI) treatment is known to have an effect after 2 weeks. Therefore, 8 weeks should be sufficient to detect any changes in symptoms and quality of life. The role of TRANSFoRm in this study is to identify prevalent and incident cases of GORD, randomise patients to on-demand or continuous use of PPI and follow up these patients using mobile or web applications and eCRF completed by GPs at primary care visits. Further details about the clinical study will be provided in a separate publication.

### Aim and objectives

The study described in this protocol aims to assess the effectiveness of TRANSFoRm in patient recruitment compared to standard GP-led opportunistic recruitment. The study hypothesis is that TRANSFoRm will increase patient recruitment by 15%, from 20% to 35%, compared to standard practice.

The objectives of the study are:To evaluate the effectiveness of TRANSFoRm in recruiting patients to clinical trials.To assess its effectiveness in collecting complete baseline and follow-up data.To compare the costs of recruitment in the TRANSFoRm and control arms.To explore practitioner and patient experience and acceptability of the system.

## Methods/design

### Trial design

We plan to conduct a 24-week, multi-centre, parallel-arm cluster randomised controlled trial of TRANSFoRm recruitment compared to GP-led opportunistic recruitment. The intervention arm will use the TRANSFoRm tools for participant recruitment, baseline data collection and follow-up. The control arm will rely on standard GP-led recruitment using web-based CRFs for baseline data collection and paper-based questionnaires for follow-up. The study will run in five countries (United Kingdom, The Netherlands, Belgium, Poland, and Greece) with eight primary care centres in each country, giving a total of 40 centres. Of these, 20 will be randomised to the TRANSFoRm arm and 20 to control on a 1:1 allocation ratio. Potentially eligible participants will be identified and recruited using TRANSFoRm or standard GP recruitment, with the hypothesis being that TRANSFoRm will yield 35% recruitment rate compared to 20% for the standard method. Participants will be finally randomised to on-demand or continuous use of PPI as part of the clinical protocol for the GORD study (Figure 3).

**Figure 3 Fig3:**
[figure not shown]
**Study design—a two-arm cluster randomised controlled trial comparing TRANSFoRm with standard GP-led opportunistic recruitment.**

### Participants

The intervention will be implemented at the primary care centre level. To be eligible for participation, primary care centres should use an EHR system compatible with TRANSFoRm, provide written agreement to participate in the GORD study, agree to participate in whichever arm they are randomly allocated, have a list size of over 2,000 patients and be able to identify at least 100 eligible participants over the 16-week recruitment period. Primary care centres lacking an appropriate EHR system or centres that have migrated from paper-based record keeping within the last 12 months will be excluded. Primary care centre characteristics, such as list size and GORD prevalence, will be gathered from GP database audit to inform recruitment. Local project partners will liaise with the study coordinator to recruit care centres that meet the above criteria.

Study participants will be GPs located in primary care centres receiving the TRANSFoRm intervention or standard recruitment method, and GORD patients using the web/mobile- or paper-based method for recording self-reported data. To be eligible for participation, patients should be GORD cases with heartburn and/or acid regurgitation that need PPI treatment, aged 60–85. Pregnant women, patients with a myocardial infraction within 6 months of the study commencement or patients with serious comorbidity will be excluded from the study.

Informed consent will be sought from all sites. Primary care centres will provide informed consent as a unit. This may vary from all GPs signing the consent form to one GP being authorised to sign on behalf of the centre. Patients will consent in accordance with the requirements of the GORD trial. The participating centres will receive €17 compensation for each correctly enrolled patient. Patients will not receive any incentive for taking part. Participants are not expected to experience any harm as a result of their participation in the evaluation study, as their involvement is restricted to completing the PROM questionnaires. Despite including health information, it is unlikely that these questionnaires will address any sensitive issues.

### Setting

We aim to recruit 40 urban, suburban and rural primary care centres in and around five European sites: London (United Kingdom), Utrecht (The Netherlands), Antwerp (Belgium), Wroclaw (Poland) and Heraklion-Crete (Greece). A dedicated member of the study team will liaise with local coordinators in each country to recruit eligible practices. Detailed practice characteristics will be provided in future publications.

### Intervention and control

Primary care centres allocated to the intervention arm will use the TRANSFoRm tools for participant recruitment, baseline data collection and follow-up. When visiting their GP, potentially eligible patients will be flagged by the system so that their GP can check for the first set of inclusion and exclusion criteria and, if appropriate, collect informed consent for further screening. Next, clinician-reported outcome measures (CROM) data from the patient’s health record will populate fields into the patient’s eCRF. The system will notify the GP about any missing data. Upon GP approval, the system will randomise patients to on-demand or continuous use of PPI. Participants will then receive information on how to fill out the PROM fields on their smartphone or the web. When participants return for the follow-up visit after 8 weeks, as stipulated in the clinical protocol, the CROM data is activated; the GP checks all prefilled fields and adds any missing data. If the participant does not attend the second visit, the GP will receive a reminder. PROM data is provided by the participants within 3 days from the second visit using the mobile/web application. Participants will receive reminders 2, 3 and 4 days after the visit, if the self-reported data is not provided.

Control centres will use standard GP-led opportunistic recruitment and data collection methods. Patients will be identified as potentially eligible by their GP after checking their health record during the consultation. The GP will check for the exclusion criteria, and, if the patient is still eligible, they will provide them with information about the study. Upon patient consent, the GP will complete the CROM fields and the patient will be randomised to on-demand or continuous use of PPI following the randomisation design for the GORD study (i.e. block randomisation containing four blocks based on age and gender). The patient will receive a questionnaire to complete either at the primary care centre or at home. Patients will be followed up using paper-based questionnaires.

### Primary outcome

The primary outcome measure is the proportion of eligible patients successfully recruited using the TRANSFoRm method compared to standard GP-led opportunistic recruitment. A record of all identified, screened and successfully recruited patients will be kept using data from GP systems. The percentage of those recruited in the trial will be compared to identify whether TRANSFoRm yields a higher number of recruited patients compared to standard GP recruitment.

### Secondary outcomes

Secondary outcomes will include the proportion of GORD cases recruited with complete baseline and follow-up data, as well as the proportion of those giving informed consent to participate but later withdrawing from the study. All electronic or paper-based CRFs completed by the recruited patients in each group will be reviewed, and retention data will be collected to examine whether there is a difference in the percentage of patients with complete data and the numbers of participants withdrawn or lost to follow up among the two arms.

### Economic evaluation

A cost analysis will estimate the costs of recruitment using the TRANSFoRm system and the standard method. A similar approach was adopted in a previous study comparing recruitment methods across sites [12]. The analysis will focus on the direct costs incurred to the primary care centre during the implementation and operation phases. Patient and third party costs will not be included. Trial administration costs, including labour and material costs and personnel time spent will be identified and combined with recruitment data to model the average cost per site and enrolled participant. Non-recurring costs will spread out over 15 years and will be discounted at a 3.5% rate. If TRANSFoRm results in increased recruitment but is also more costly, the cost per additional participant will be estimated to assess whether this excess cost is acceptable.

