The evaluation will include patients with GORD, and otherwise eligible for the study, for whom a single clinic appointment was made during the recruitment period. This measure guards against the possibility that participating centres embark on an active programme of recruitment of potential participants rather than, as instructed, relying on opportunistic presentation. Local EHR and appointment datasets will be used to validate this process. An in-depth audit will be undertaken of any centre where the appointment rate lies more than two standard deviations from the within-country mean. In all other centres, a random selection of appointments created for GORD patients during the recruitment period will be audited by an evaluation team member in liaison with a local collaborator.

The study has some weaknesses. The scope of the economic analysis is limited to the care centre level. This practically means that we cannot assess the costs and benefits for all stakeholders in the project. However, patients will be able to provide qualitative feedback on the impact of the TRANSFoRm tools in follow-up interviews and a TAM survey. Another limitation is that the study timeline is relatively short to evaluate the long-term effects of the intervention, despite being sufficient to recruit the required number of participants and collect data to explore the evaluation aims. Considering that technology adoption is a complex process [22,23], the time from implementation to evaluation is relatively short to assess the performance of the TRANSFoRm system.

The protocol provides a reproducible process for conducting a summative evaluation of the TRANSFoRm system based on the GORD clinical trial. The evaluation study focuses on assessing the effectiveness of TRANSFoRm-supported recruitment and follow-up in primary care research compared with standard GP-led opportunistic recruitment. The study should provide useful information about the use of information technology to improve the efficiency, time and costs of recruitment and follow-up in primary care and is expected to provide an evidence base for future eHealth-supported recruitment initiatives.

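### The cost comparison spreads one-off costs over a single, unsupported 15-year life, which could favour TRANSFoRm if its set-up costs are larger and its real life is shorter

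*Protocol article*

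**What the plan says.** Comparing recruitment costs between the arms is one of the four objectives (protocol article, Aim and objectives). The Economic evaluation section sets out how:

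- Scope: "The analysis will focus on the direct costs incurred to the primary care centre during the implementation and operation phases". Also: "Patient and third party costs will not be included".
- Output: labour, material and time costs are "combined with recruitment data to model the average cost per site and enrolled participant".
- One-off costs: "Non-recurring costs will spread out over 15 years and will be discounted at a 3.5% rate".
- Decision rule: "If TRANSFoRm results in increased recruitment but is also more costly, the cost per additional participant will be estimated".

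The section gives no reason for 15 years, no useful life for the tools, no amount of one-off cost in either arm, and no rule for how much of a yearly charge falls on the trial. On timing, the Trial design section says "We plan to conduct a 24-week, multi-centre, parallel-arm cluster randomised controlled trial", and the description of the clinical trial workflow says the GORD study "will involve 16-week recruitment and 8-week follow-up". The only other 15-year figure in the article is the data-archiving period in Handling and storage of data, which has no bearing on how long the tools stay in use.

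**The concern.** The write-off period is an assumption, and it feeds directly into both cost outputs. A longer period makes the charge to any one study smaller. It helps most whichever arm has the larger one-off costs.

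That arm is plausibly TRANSFoRm. Intervention centres take on new alert, eCRF and record-linkage tools. Control centres recruit in the standard way, with web-based CRFs and paper questionnaires. Both arms need a compatible EHR system, so that cost is common to them.

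The cost per additional participant is calculated only where TRANSFoRm recruits more and also costs more. The assumed life can therefore affect the size of the cost difference, possibly its sign, and whether that last result appears at all.

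**Working it through.** **Inputs from the protocol article:** rate r = 3.5% and life n = 15 years (Economic evaluation); trial length 24 weeks (Trial design); recruitment period 16 weeks (clinical trial workflow).

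**Assumptions:** alternative lives of 3 and 5 years, and the share f of one year's charge that is put to the trial. The article gives neither. It also states no percentage of set-up cost charged to the trial, so there is no figure of its own to reproduce.

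**Step 1: yearly charge.** Annuity factor A(n) = [1 − (1 + r)^−n] / r; yearly charge a(n) = 1 / A(n).

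| Life | A(n) | a(n), % of set-up cost | Ratio to 15 years |
|---|---|---|---|
| 15 years | 11.517 | 8.7% | 1 |
| 5 years | 4.515 | 22.1% | 11.517 / 4.515 = 2.6 |
| 3 years | 2.802 | 35.7% | 11.517 / 2.802 = 4.1 |

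**Step 2: charge to the trial.** This is f × a(n). The share f cancels in the ratios, so 2.6 and 4.1 hold for any f.

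| Share f | 15 years | 5 years | 3 years |
|---|---|---|---|
| 16/52 | 2.7% | 6.8% | 11.0% |
| 24/52 | 4.0% | 10.2% | 16.5% |
| One full year | 8.7% | 22.1% | 35.7% |

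**Step 3: other readings of the sentence.**

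- Straight line without an annuity, at 15 years: 6.67% for a year, 3.08% for 24 weeks, 2.05% for 16 weeks. The ratios are then 15/5 = 3 and 15/3 = 5.
- If instead all 15 equal slices are discounted and summed, the charge is 11.517 / 15 = 77% with end-of-year slices, or 79% with start-of-year slices. At 5 years the end-of-year figure is 4.515 / 5 = 90%. The gap is smaller but runs in the same direction.

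The sentence as written therefore allows a charge of about 2% to 9% on the time-share readings, or 77% to 79% on the summed reading.

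**Step 4: when the sign of the cost difference changes.** Let D be TRANSFoRm's extra one-off cost per centre over control, and s its saving in running cost per centre during the trial. TRANSFoRm costs more per site when f × a(n) × D > s. With f = 24/52, that means s below 4.0% of D at 15 years, 10.2% at 5 years and 16.5% at 3 years. If s lies between 4.0% and 10.2% of D, TRANSFoRm is cheaper per site at 15 years but dearer at 5. The break-even life is the n at which a(n) = s / (f × D). The article gives neither D nor s.

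**Step 5: scale per recruit (illustration only).** Take 100 eligible patients per centre and 35% recruitment (Sample size), so 35 recruits. With f = 24/52, each 1,000 euro of set-up cost (assumed) adds 1.1 euro per recruit at 15 years, 2.9 at 5 and 4.7 at 3. Charged in full it adds 1,000 / 35 = 28.6 euro. These figures scale in proportion: at an assumed 3,000 euro they are 3.4, 8.8, 14.1 and 85.7 euro.

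**The case against.** The strongest reply is that spreading the cost of a reusable system beyond one study is the purpose of annuitisation, so a life longer than the trial is no error. The rule covers both arms, and the control arm also uses a web-based system. Only costs borne by centres count, and the article does not show that centres pay for the software or its connectors, which the project team developed. If one-off centre costs are small or similar between arms, the effect largely disappears. The section also says a similar approach was used in an earlier comparison of recruitment methods, though not whether the 15 years comes from it. Further sensitivity analyses may stand in the full plan.

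Most of this stands, and it limits the point. A reader might infer any of the following, but the article does not support them:

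- **The trial is charged 4% of set-up cost.** This needs pro-rating to 24 of 52 weeks, which the plan does not specify.
- **The comparison is tilted towards TRANSFoRm before data are seen.** This needs larger one-off centre costs in that arm and a real life under 15 years. The article establishes neither.
- **Costs are understated 25-fold against the outlay.** Full charging (100 / 4.0) gives the tools no residual value after 24 weeks. It is an upper bound, not a benchmark.
- **The Discussion undermines a 15-year life.** Its remark that "the time from implementation to evaluation is relatively short to assess the performance of the TRANSFoRm system" concerns adoption time, not useful life. The same paragraph calls the timeline sufficient for the evaluation aims.

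The reply does not supply a reason for the 15 years. The article commits to that one figure, so this is not merely a detail left to another document. Restricting the ratio to the case of more recruitment at more cost is ordinary practice and is not criticised here.

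**Conclusion.** The point holds in a conditional form. The 15-year life is fixed without support in the article, and the rule for charging it to the trial is ambiguous. Under annuitisation at 3.5%, shortening the life to 5 or 3 years raises the charge 2.6-fold or 4.1-fold, independent of the time share. Whether this favours TRANSFoRm, and by how much in euros, depends on one-off centre costs per arm and on the real life of the tools. The article gives neither, and the 3- and 5-year lives are assumptions used to show the range.

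The consequence is confined to the cost objective: cost per site, cost per enrolled participant, and possibly whether a cost per additional participant is reported. It is a cheap improvement, not a threat to the trial's main conclusion.

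**What to change.** In the Economic evaluation section:

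1. Justify the 15-year life for the tools at a centre, or replace it with a life that can be justified. The 3- and 5-year figures here are scenarios and are not offered as a new base case.
2. State how the yearly charge is applied to the trial: the share of a year used, and whether costs are annuitised or written off in a straight line.
3. Pre-specify the cost comparison at 3, 5 and 15 years, with full within-trial charging as an upper bound.
4. In every scenario, report the cost difference between arms. Also report the life at which the arms break even.
5. Report cost per additional participant where TRANSFoRm recruits more and costs more. Where it recruits more and costs less, report dominance, since the ratio is then negative and has no useful meaning.

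The cost is a few more rows in the cost model and no new data. The possible downside is a less favourable cost result for TRANSFoRm.
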